**7. Research Methods and Outcomes**

Each of the 120 households will be visited monthly for water quality testing and household questionnaires. Specifically, the research methods will include:

- Household surveys, observations, and focus group discussions to evaluate use, longevity, and acceptability (objective 1)
- Routine water quality testing of source, treated, and stored water to evaluate microbiological performance (objective 2)
- Regular disease surveillance, including household visits to assess reported diarrhoea, changes in weight and hospital admissions for diarrhoea (objective 3)

*Use, Longevity and Acceptability*

Previous research has suggested that a principal reason for failure to achieve the potential health gains from HWTS interventions is sub-optimal adoption—particularly exclusive use by the most vulnerable segments of the population. In this RCT, use will be the principal outcome. Each filter unit will be encoded with a number and the date distributed will be recorded. The investigator will develop criteria for assessing use and a set of indicators based thereon (e.g., filter mounted for use in the household, filter reported to have been used on the day of the visit or the previous day, storage vessel contains water that is reported to have been treated, and microbiological quality of water is at least 1 log lower in TTC than source water). Thereafter, the investigator will determine whether the device is in use during each household visit using the specified indicators that combine reporting and observations. Furthermore, approximately 10% of the filters will include flow meters that record the quantity of water that has been run through the filter to objectively measure filter use. If the device is not being used at all, the investigator will record the reasons according to the mother. If the device is no longer in use due to clogging, the investigator will record the date it clogged and attempt to restore use by normal cleaning. If service cannot be restored, the investigator will replace the cartridge or other failed component and note the change.

Information will also be gathered on use of filtered water to make replacement feeds for young children through household questionnaires and observations. Mothers will be asked during household visits about the water given to young children directly or added to other drinks or food consumed by young children. Observations may be included on approximately 20%-50% of households to examine water practices concerning infant feeding.

The acceptability of the technology will be evaluated by conducting household surveys, household observations, and focus group discussions (FGDs). Households will be interviewed monthly through household questionnaires, and additional information will be gathered on acceptability after approximately 4 and 8 months. Mothers will be asked to participate in FGDs at the end of the study to provide feedback on the technology including perceived benefits and limitations.

On two occasions during the course of the study, about a quarter of the households will be visited by investigators to obtain more extensive information about providing children <2 years food and water. During these visits, we will be talking with the primary caretaker of the child and will also be asking her to demonstrate certain practices and allowing the investigator to spend time in the home observing the practices directly. Particularly, observations will explore exposure pathways for contaminated water, and for the intervention households, to what extent the filtered water is given to young children.

*Microbiological Performance*

The performance of the HWTS technology will be evaluated by bacteriological water quality testing. Water samples will be taken during unannounced household monthly visits of all households. For households that have not received the filter, water samples will be collected of i) source water and ii) stored drinking water. For households that have received the filter, water samples will be collected of i) source water (influent water), ii) effluent water out of the filter, and iii) stored drinking water. Source drinking water will be collected to determine technology performance by comparing effluent and influent water quality. For the stored drinking water, the householder will be asked if there is any drinking water in the house at that moment and samples will be collected from the vessel that the householder identifies as being used at that moment to fill a cup or glass for drinking.

All samples for analysis will be collected in sterile Whirl-Pak™ Bags containing a tablet of sodium thiosulfate to neutralize any disinfectant. Samples will be placed on ice and processed within 4 hours of collection to assess levels of thermotolerant (faecal) coliforms. Microbiological assessment will be performed using a DelAgua field incubator (University of Surrey) in accordance with the Standard Methods (Eaton, Franson et al. 2005).

*Diarrhoea Prevalence*

This study is designed to use two techniques on diarrhoeal surveillance: i) conventional report of diarrhoea prevalence and ii) a novel technique using weight-for-age z-scores (WAZ) as a proxy for diarrhoea. Diarrhoea prevalence will be recorded for the children <2 years and for all household members as longitudinal prevalence from 7-day recalls by the mothers. Diarrhoea will also be objectively assessed by recording hospital admissions for diarrheal disease. Longitudinal prevalence (the proportion of days with diarrhoea divided by the number of days under observation) is a preferred metric for assessing diarrhoea because it is a strong predictor of long-term health outcomes (Morris, Cousens et al. 1996). In the cross-sectional study, it was determined that a 7-day recall was appropriate for the study population. Diarrhoea will either be defined according to the WHO definition of 3 or more loose stools within a 24-hour period (WHO 2005), or using a local definition if found to be comparable. Diarrhoea will be assessed during household visits approximately every month, totalling 12 visits over the course of one year. Feeding practices for the children <2 years will be included in household questionnaires which may affect diarrhoea prevalence.

A novel approach for measuring diarrhoea is to use weight-for-age z-scores (WAZ) as proxy (Schmidt, Boisson et al. 2009). Objective markers for diarrhoea are needed to avoid potential bias that may occur during in conventional self-report measurements. Short-term changes in WAZ have been found to be strongly associated with diarrhoea prevalence. In this study, we will pilot using WAZ to measure the effect of the intervention. Children <2 years will be weighed using baby scales during monthly visits, and date of birth will be verified on the child’s health card to calculate WAZ.

### 8. Data Analysis

Specific endpoints will be analysed corresponding to each objective.

| Objective #1 | - Percent of households using the filters during the entire study - Percent of households using the filters for children <2 years - Percent of households that had technical problems with the filters (clogging or breaking) - Qualitative feedback on filter acceptability |
| --- | --- |
| Objective #2 | - Median and range of TTC concentration in coliform forming units (CFUs) per 100 mL, of   - Source water   - Filtered drinking water   - Stored drinking water - Mean and range percent removal of TTCby LifeStraw Family |
| Objective #3 | - Relative risks of reported diarrheal prevalence and diarrheal hospital admissions in children < 2 and all household members, comparing intervention and control - Weight gain over 12 months of the study, using WAZ as a proxy for diarrhoea |

Survey data will be collected with paper questionnaires, entered into EpiInfo, and analysed using Stata10. Water quality data will be entered into Excel and analysed using Stata10. The statistical analysis will account for clustering by households as necessary, and intracluster correlation of repeated measurements on the same individual (Hayes and Moulton 2009). A logistical regression model will be fit and a multivariable analysis will adjust the model for potential confounders (age, socioeconomic status, etc) to compare intervention and control populations.

After study completion, a summary of the results will be communicated to all study participants at a meeting called for that purpose. Study participants in the control group will receive a LifeStraw Family filter. A full research report detailing the results of the investigation will be distributed to the ethics committees.

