### 1. Background

Contaminated drinking water is a leading cause of morbidity and mortality in low-income settings. Safe drinking water is of particular concern for HIV-positive mothers since many HIV-infected Zambian women choose replacement feeding and early cessation of breastfeeding of infants to minimize the risk of transmission of the virus (CIGNIS study results; S Filteau, L Kasonka et al., submitted). In resource-poor settings, HIV-positive mothers must choose between breastfeeding their infant and potentially transmitting HIV, or formula feeding their infant and thereby risking diarrhoeal disease morbidity and mortality. However, the extent to which the drinking water actually being used by this population is safe, and what steps could be taken to ensure the microbiological quality of such water, is largely unknown.

Our previous work in Zambia found that HIV-positive mothers with children <2 years would potentially benefit from an intervention that encourages HIV-positive mothers to treat their water at the household level before using it for their young children and all household members. In a cross-sectional study of 254 households, we found that 26% of children <2 years had diarrhoea in the past week, 53% of children <2 years received supplemental water in the past 2 days, and 70% of households had faecally contaminated drinking water. This proposed study aims to assess a household water treatment technology in the form of a randomized controlled, trial.

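### The diarrhoea endpoint is a relative risk, but the only between-arm model named is logistic regression, with no stated route from its odds ratios to a relative risk

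*Protocol*

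**What the plan says.** Protocol section 8 sets the Objective 3 endpoint as "Relative risks of reported diarrheal prevalence and diarrheal hospital admissions in children < 2 and all household members, comparing intervention and control". The text under the endpoint table then names one model for comparing the two populations: "A logistical regression model will be fit and a multivariable analysis will adjust the model for potential confounders". No log-binomial or Poisson model is mentioned, nor any standardisation of the logistic fit.

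Section 7 defines the diarrhoea measure as longitudinal prevalence, "the proportion of days with diarrhoea divided by the number of days under observation", collected as "longitudinal prevalence from 7-day recalls by the mothers" at about 12 monthly visits. Section 1 gives the only background rate: "26% of children <2 years had diarrhoea in the past week", from the earlier cross-sectional study.

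On correlation, section 8 says "The statistical analysis will account for clustering by households as necessary". The same sentence goes on to commit, without that qualifier, to handling correlation between repeated measurements on one individual. Section 6 allocates the intervention by household.

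**The concern.** The protocol fixes both the effect measure and the model, and the two do not match. An analyst who follows the text literally obtains odds ratios where relative risks were promised. For a beneficial effect the odds ratio lies further below one than the relative risk, and the distance grows with the control-arm proportion. If the adjusted odds ratio fills the place reserved for the relative risk, the filter looks more protective than it is.

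The protocol also leaves open whether the logistic outcome is a yes/no week or a count of days out of days recalled. These have different control proportions, so the size of the distortion depends on which is meant.

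**Working it through.** **Plan's own figure.** The protocol gives no effect size, power or expected result for diarrhoea, so there is nothing to reproduce on this endpoint. Its only design calculation, 60% use with a 95% interval of 50–70% from 100 households, is reproduced (0.60 ± 1.96 × √(0.60 × 0.40/100) = 50.4% to 69.6%) and does not bear on this point.

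**Inputs.**
- Control proportion if the outcome is any diarrhoea in the week: 0.26 (section 1, children under two), assumed to apply to this trial's control arm.
- Control proportion if the outcome is days ill out of days recalled: not given, but bounded by the 7-day window. If each affected child is ill on one day, it is 0.26 × 1/7 = 0.037. If each is ill on all seven, it is 0.26 × 7/7 = 0.26.
- True relative risk: not given; 0.50, 0.60 and 0.75 are assumed for illustration.

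**Formula.** With control proportion p0 and intervention proportion p1 = RR × p0, OR = [p1/(1 − p1)] / [p0/(1 − p0)].

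**Worked case, weekly outcome.** p0 = 0.26 and RR = 0.60 give p1 = 0.156. OR = (0.156/0.844)/(0.26/0.74) = 0.1848/0.3514 = 0.526. Read as a relative risk, a 40% reduction becomes 47%.

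**Worked case, lower bound for days.** p0 = 0.0371 and RR = 0.60 give p1 = 0.0223. OR = 0.0228/0.0386 = 0.591. A 40% reduction becomes 41%.

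**Range.**

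| Control proportion | OR at RR 0.50 | OR at RR 0.60 | OR at RR 0.75 | Gap at RR 0.60 (points) |
|---|---|---|---|---|
| 26% (week; upper bound for days) | 0.425 | 0.526 | 0.689 | 7.4 |
| 15% (assumed) | 0.459 | 0.560 | 0.718 | 4.0 |
| 10% (assumed) | 0.474 | 0.574 | 0.730 | 2.6 |
| 5% (assumed) | 0.487 | 0.588 | 0.740 | 1.2 |
| 3.7% (lower bound for days) | 0.491 | 0.591 | 0.743 | 0.9 |
| 2% (assumed, rare event) | 0.495 | 0.595 | 0.746 | 0.5 |
| 1% (assumed, rare event) | 0.497 | 0.598 | 0.748 | 0.2 |

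The last two rows indicate what to expect for hospital admissions if they are rare; the protocol gives no rate for them, nor for diarrhoea in all household members. The table concerns unadjusted odds ratios. A covariate-adjusted odds ratio need not equal these values even in a perfectly balanced trial, which is a further reason to state the target measure.

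**The case against.** Four points can be made in the plan's defence.

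1. *Logistic regression can deliver what is promised.* A reader might infer that it can yield neither a relative risk nor an analysis of days. That is too strong. A grouped-binomial logistic model takes days ill out of days recalled, and marginal standardisation of a logistic fit gives an adjusted relative risk. What stands is that the protocol states neither step, so the model need not be discarded but the route must be named.

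2. *The 26% is not the endpoint's prevalence.* It is a weekly any-diarrhoea figure, while section 7 defines a proportion of days. A reader who carries the 7-point gap over to longitudinal prevalence goes beyond the document. This objection stands, and it reduces the gap at a relative risk of 0.60 to somewhere between about 1 and 7 points.

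3. *Nothing says an odds ratio will be labelled a relative risk.* True: the harm is conditional, and a statistical analysis plan, not available here, might resolve it. But the mismatch lies between two things the protocol itself fixes, not in detail it leaves for later.

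4. *Clustering is covered.* A reader might take the qualifier in "The statistical analysis will account for clustering by households as necessary" to make all correlation adjustment optional, including the 12 or so measurements per person. The rest of that sentence rules this out, since repeated measures are committed to without qualification. For the index children, usually one per household, household clustering beyond the repeated measures adds little. Nor does the text say clustering will be dropped for all household members. There the design plainly calls for it, so the qualifier is a minor looseness and no more.

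**Conclusion.** The mismatch is real and sits in the current text of section 8: a relative-risk endpoint, a logistic model and no link between them. Its direction is certain: for any protective effect, an unadjusted odds ratio read as a relative risk exaggerates benefit. Its size depends on the outcome modelled. At a true relative risk of 0.60 it is 7.4 points for any diarrhoea in the week at 26%, between 0.9 and 7.4 points for day-based prevalence, and probably negligible for admissions if they are rare. These figures assume that the earlier study's 26% carries over to the control arm and that the odds ratio is in fact reported or read as a relative risk.

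The point concerns the third objective. Use is the principal outcome and the sample size rests on it, so neither is touched, and the direction of any diarrhoea effect would not change. It should be corrected because the protocol would otherwise lead to a number other than the one it promises.

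**What to change.** In section 8, state the outcome as days with diarrhoea out of days recalled, and name one of two routes to the relative risk:

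- a log-link model, for example modified Poisson with generalised estimating equations and the log of days recalled as offset; or
- the logistic model already planned, followed by a marginally standardised relative risk with its confidence interval.

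For the all-household-members analysis, state that standard errors are clustered on household, the randomised unit, without a qualifier. Keep the existing commitment on repeated measurements. If hospital admissions are modelled with a person-time offset, call the result a rate ratio and amend the endpoint table to match.

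The cost is a few lines of analysis wording. Design, visits, sample size and principal outcome stay as they are. The one condition is that the recall question records the number of days ill, as the section 7 definition already requires. If only a yes/no answer is collected, the outcome is weekly prevalence and should be named as such; the 26% row then applies and the case for reporting a relative risk explicitly is stronger.

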**3. Sample Size**

One hundred and twenty households will be followed for one year. The sample size of one-hundred households is based on the primary outcome (adoption) and is based on an estimated 60% of the study population satisfying the conditions for use, with a standard of 0.05, for a 95% confidence interval of 50-70%. An additional 20 households of HIV-negative mothers will be included to reduce stigma of the study. The study population will be followed for one year to account for seasonal variability in water quality.

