**5. Study Population and Recruitment**

Study participants will be recruited through the community health clinic for the catchment area or areas. In our cross-sectional study, it was particularly efficient to recruit through ART programs, nutrition programs, and the under-five clinics at the community health centres; depending on the health centre(s) chosen, we may use similar recruitment methods. Women will be eligible to participate in the study if (i) they report that they are HIV-positive based on clinical testing, (ii) they currently have a child age six months to one year at the beginning of the study, and (iii) they reside in a household located in the designated peri-urban area(s) in or around Lusaka, Zambia, (vi) drinking water of poor quality. HIV-status of mothers will be confirmed by the child’s exposure status (‘exposed’ or ‘unexposed’) on the child’s health record. Women that are interested in participating will be asked for consent and household location information will be obtained for follow-up. It is possible that some of the same HIV-positive mothers from our cross-sectional study will be included in the RCT. In order to reduce stigma, we plan to include an additional 20 HIV-negative mothers (10 in intervention group and 10 in control). These mothers will also be recruited from the selected community health clinic(s). We will be asking about infant HIV-status if known, though this will not be required for participation. Participating mothers will be reminded that HIV-testing of children is available in Zambia free-of-cost, including PCR testing from 6 weeks. If mothers subsequently choose to have their children undergo HIV testing, we will ask that they contact us with the results.

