### 6. Baseline Survey and Intervention

*Baseline survey and randomization*

Before the water filter is distributed, a baseline survey will be conducted of the recruited participants. The baseline study will include information on demographics, sanitation facilities, hygiene practices, water sources and treatment practices and other factors that could potentially impact the outcomes of interest. After the baseline survey, the intervention will be randomly allocated to half of the recruited participants. Participating households will be numbered consecutively and then allocated into the two groups using a random number generator. Households that do not receive the filter at the beginning of the study will receive the filter at the end of the study. Households will receive training on how to use and maintain the filter prior to receiving the intervention.

*The Intervention*

The intervention consists of the Lifestraw Family filter for household water treatment and a storage container to encourage safe water storage of treated water. The LifeStraw Family is a HWTS filtration technology shown to remove microbial contamination from drinking water and to be acceptable to users. The device was chosen because it has been shown to be effective against the full array of microbial pathogens and to have a longevity that exceeds one year (Clasen, Naranjo et al. 2009). Developed by Vestergaard Fransen SA, LifeStraw Family is a new household-based gravity filter system that uses ultrafiltration mechanisms to remove pathogens. The filtration unit consists of a hollow-fibre cartridge of 20 nm diameter pore size. Untreated water is poured into a 2.5L container, flows down a 1m long tube designed to provide head pressure, and through the ultrafiltration cartridge where it is dispensed via tap. The cartridge is also equipped with a backwash inlet to facilitate cleaning of the cartridge, thus minimizing clogging and improving longevity. The flow rate of the device averages at 8.8L/hour (over design life of 18,000L with periodic cleaning and backwashing),(Clasen, Naranjo et al. 2009) and the flow shuts down when the hollow-fibres are exhausted, indicating when to replace the cartridge.

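### Diarrhoeal admissions are compared between arms, but the only model named is a multivariable logistic regression, which about 60 index children per arm may be too few to support; report admissions as exact, descriptive figures (minor)

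*Protocol*

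**What the plan says.** The Objective #3 row of the table in Protocol section 8 lists "Relative risks of reported diarrheal prevalence and diarrheal hospital admissions in children < 2 and all household members, comparing intervention and control". The text below the table says that clustering and repeated measurements will be allowed for, and then names one model: "A logistical regression model will be fit and a multivariable analysis will adjust the model for potential confounders (age, socioeconomic status, etc". Its stated purpose is to compare the intervention and control populations. No other between-arm model is named, and no endpoint is excluded from this one.

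Section 7 gives admissions a particular role beside the 7-day recall: "Diarrhoea will also be objectively assessed by recording hospital admissions for diarrheal disease".

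The numbers come from sections 3, 5 and 6. Section 3: "One hundred and twenty households will be followed for one year". Section 6: "the intervention will be randomly allocated to half of the recruited participants". Section 5 requires of each mother that "they currently have a child age six months to one year at the beginning of the study". The sample size rests on filter use alone. The protocol gives no expected admission risk.

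**The concern.** Admission during the year is a yes/no outcome compared between arms, so the natural reading of section 8 sends it to the adjusted logistic model. Maximum-likelihood logistic regression behaves badly with few events. If one arm has no admissions, the arm coefficient has no finite estimate. If there are some in each arm but only a few per model parameter, the odds ratio tends to be biased away from 1 and its Wald interval is untrustworthy.

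The protocol offers admissions as an objective check on recalled diarrhoea in a trial where families know whether they have a filter. An adjusted ratio resting on a handful of events, or a model that fails to fit, could be taken as confirming or contradicting the recalled result when it does neither. If the method is left until the counts are known, the choice of model may also be swayed by them.

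**Working it through.** **The plan's own figure.** Section 3 derives 100 households from 60% use. SE = √(0.60 × 0.40 / 100) = 0.049, and 0.60 ± 1.96 × 0.049 gives 50.4% to 69.6%, which matches the stated 50–70%. This concerns use only and says nothing about admissions.

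**Inputs**
- Households: 120, including the 20 HIV-negative ones, followed for one year (section 3).
- Allocation: half to each arm (section 6), so 60 per arm.
- Index children: at least one per household (section 5), so about 60 per arm.
- Control admission risk p over one year: not in the protocol. Assumed range 2%, 5%, 10%, 15%.
- True relative risk: assumed 0.7.

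**Expected admissions.** 60p + 60(0.7p) = 102p.

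**Chance that at least one arm has none.** With a = (1 − p)^60 for control and b = (1 − 0.7p)^60 for intervention, the chance is 1 − (1 − a)(1 − b).

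| Assumed control risk | Expected admissions, both arms | a | b | Chance of an empty arm |
|---|---|---|---|---|
| 2% | 2.0 | 0.298 | 0.429 | 60% |
| 5% | 5.1 | 0.046 | 0.118 | 16% |
| 10% | 10.2 | 0.002 | 0.013 | 1.5% |
| 15% | 15.3 | <0.001 | 0.001 | 0.1% |

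**Which coefficient fails.** Trials of 60 v 60 children were simulated at the same four risks, with a check for separation.
- Arm, age and a continuous socioeconomic score: some coefficient was not finite in about 60%, 16%, 1% and 0% of trials. Within simulation error this is the empty-arm chance.
- Arm, one continuous covariate, three socioeconomic-quartile indicators and one binary covariate: about 98%, 74%, 28% and 7%. The excess comes from quartiles or categories with no admissions, not from the arm term.

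The protocol does not say how socioeconomic status will be coded, so the second set of figures depends on an assumption and does not measure the treatment estimate.

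**Events per parameter.** With arm plus five covariate terms (six coefficients), 10.2 / 6 = 1.7 and 15.3 / 6 = 2.6, or roughly two. With arm, age and one socioeconomic score (three coefficients), 10.2 / 3 = 3.4 and 15.3 / 3 = 5.1, still few.

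**What an exact analysis would show.** Given the total, intervention admissions are binomial. With equal person-time, a Clopper-Pearson limit π converts to a rate ratio as π / (1 − π).
- 3 control v 2 intervention: π from 0.053 to 0.853, rate ratio 0.06 to 5.8.
- 6 v 4: π from 0.122 to 0.738, rate ratio 0.14 to 2.8.
- 3 v 0: upper π = 1 − 0.025^(1/3) = 0.708, so the rate ratio is 0 with upper limit 2.4.

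The last case has no finite logistic arm coefficient, yet the exact method gives a usable result.

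**All household members.** At an assumed five people per household (300 per arm), ignoring clustering, with relative risk 0.7:
- 1% control risk: 300 × 0.01 × 1.7 = 5.1 admissions. a = 0.99^300 = 0.049, b = 0.993^300 = 0.122, empty-arm chance 16%.
- 2% control risk: 10.2 admissions. a = 0.98^300 = 0.002, b = 0.986^300 = 0.015, empty-arm chance 1.7%.

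**The case against.** The strongest reply is that the protocol does not commit admissions to this model. The Objective #3 row promises relative risks, which can be reported unadjusted. The logistic sentence is general and cannot cover every endpoint, since weight-for-age z-score and coliform counts are not binary. Matching models to endpoints, listing covariates and naming a sparse-data fallback are ordinary matters for an analysis plan, which is not at hand. This limits the point but does not remove it. The sentence is stated as the way to compare the arms, admission is a binary between-arm endpoint, and nothing in the protocol sends it elsewhere.

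Three stronger readings are tempting and are not supported:
- *That admissions are known to be rare, so the estimate will often be undefined.* No admission risk is documented. The only diarrhoea frequency, 26% of children under 2 in the past week (section 1), is reported illness. At 10–15% risk an empty arm is unlikely.
- *That the adjusted model would nearly always break down.* The high separation rates depend on several categorical covariates, which the protocol does not specify, and they mostly do not concern the arm effect.
- *That an empty arm leaves no estimate at all.* For the stated measure, an empty intervention arm gives a relative risk of 0 with a finite exact upper limit.

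It is also fair that the endpoint extends to all household members, where more events can be expected. But children under 2 are listed as a group of their own, so the wider group does not rescue that comparison.

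**Conclusion.** The point holds in conditional form, as a cheap improvement of minor severity. If one-year admission risk in control children is about 5% or less, the logistic arm coefficient has no finite estimate in about 16% of trials at 5% risk and about 60% at 2%. At 10–15% that failure is rare (1.5% or less), but there are only about two events per parameter with arm plus five covariate terms, so the adjusted odds ratio in children under 2 would still be unreliable.

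These figures rest on the assumed risks, a true relative risk of 0.7, one index child per household and full follow-up; the events-per-parameter figure also rests on an assumed covariate set. The severity is minor because admissions are one part of the third objective of a study described as a pilot, whose principal outcome is use of the filter. No main conclusion depends on them.

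**What to change.** Add to section 8, or to the analysis plan before outcome data are seen:
- For admissions in children under 2, report the number of admissions and the person-time by arm, with the unadjusted rate ratio (or relative risk) and an exact or mid-P 95% confidence interval, labelled descriptive.
- If an adjusted figure is wanted, use Firth's penalised likelihood with arm and child age only.
- For all household members, report the same quantities with allowance for household clustering.
- Keep the multivariable logistic model for recalled diarrhoea.

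The cost is a few lines of wording and no change to data collection, provided the follow-up time of each person is kept. Because the arms are randomised, leaving out the adjustment does not bias the comparison. The price is a wide interval and no multi-covariate adjusted figure for admissions.
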